#### **9.1.4.1.3 Dorsal Double-Layered 10% Circumferential Reduction (DD-10) Pressure Garment**

The overall approach to the DD-10 pressure garment is the same as that for the S-10 pressure garment with the main difference being that the dorsal side is simply secured using two pieces of fabrics of the same size, and then sewn together as a whole. The treatment on the thumb is simplified accordingly by not hollowing it out and measuring it along with the thumb when making the paper pattern, as shown in the Figure 6.

[figure not shown]

Figure 6. Dorsal double-layered (DD-10) pressure garment

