#### **9.1.4.3 Assessment Instruments**

The assessment instruments include Fugl-Mayer Assessment of Upper Extremity as a primary outcome measure; Box and Block Test, Modified Ashworth Scale, Visual Analogue Scale, and Disabilities of Arm, Shoulder and Hand as secondary outcome measures; and Brunnstrom Recovery Stage and Saint Louis University Mental Status as screening measures.

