#### **9.1.5 Data Collection**

Participants will be asked to read the Phase I information sheet (Appendix A) and sign the written informed consent form (Appendix L) before participating in this phase of

study.

This study will involve Therapists A and B (n: Therapist A=3; Therapist B=6) from all three participating hospitals. Therapists selected will need to have a bachelor's degree or above, and with minimum of three years of relevant work experience. The therapists will be labelled as: Therapist A, who will serve as an assessor and blinded; Therapist B, who will serve as the participant's treating therapist and blinded. The study will also include a pressure garment fabricator. The fabricator (a therapist, a researcher, or a professional tailor) must have experience in pressure garment fabrication.

Prior to the data collection, all the therapists will receive an 8-hour training on pressure garment from the pressure garment fabrication expert, whom is one of the supervisory team members. The tentative training programme is shown below:

| Time          | Content                                                                             |
|---------------|-------------------------------------------------------------------------------------|
| 08:30 – 09:00 | Registration and welcome; Introduction to the purpose of the training and programme |
| 09:00 – 10:00 | Basics of pressure garment                                                          |
| 10:00 – 10:15 | Coffee break                                                                        |
| 10:15 – 12:15 | Pressure garment measurement and pattern making I                                   |
| 12:15 – 12:45 | Education on care of pressure garment care                                          |
| 12:45 – 13:45 | Lunch break                                                                         |
| 13:45 – 14:30 | Pressure garment measurement and pattern making II                                  |
| 14:30 – 15:00 | Putting on and adjusting pressure garment                                           |
| 15:00 – 15:15 | Coffee break                                                                        |
| 15:15 – 16:30 | Simulated practical session and group exercise                                      |
| 16:30 – 17:00 | Programme summary                                                                   |

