| 17:00 – 17:30 | Q&A                                                                                 |

For randomization purposes, the researcher will generate 165 sequences that contains equal numbers of 1 (S-10), 2 (DD-10), and 3 (S-0) using a computerized software SPSS 26.0. The sequence will be store electronically. The process of data

collection will then proceed with participant recruitment. This recruitment will be done by placing posters that contain the relevant information of this study, including the study objectives, procedures, and duration alongside contact information, etc. in the three hospitals as permitted. Interested patients can contact the researcher of this study. Recruitment will also be done through recommendation made by therapists who are involved in treating stroke patients. Before enrolling into the study, potential participants will be screened using MAS, SLUMS, and BRS by Therapist A. Only those who meet the inclusion will be enrolled. Prior to the enrolment, the potential participants will need to read the information sheet (Appendix L) and sign the written informed consent form (Appendix M). Participants will be asked to complete the Demographic Form (Participant) (Appendix A).

After participant enrolment, Therapist A will report to the researcher to obtain the randomization sequence number generated using SPSS 26.0. The researcher will assign the participant into either S-10 (intervention group), DD-10 (intervention group), or S-0 (placebo group) according to the sequence list. Therapist A, a blinded therapist will then proceed with taking the baseline data or Time 1 (start of trial), including FMA, BBT, MAS, VAS, DASH, and SF-36. After that, Therapist A will take the pressure garment measurement and then, give the pressure garment measurement to the pressure garment fabricator for pressure garment custom fabrication. Upon receiving the two pairs of pressure garment (within 7 days after pressure garment measurement), the participant will try it on for 30 minutes, under the supervision of Therapist B, a blinded therapist. The participant will formally be enrolled in the study if he/she does not experience allergy, oedema, pain or any other discomfort. All participants will be asked to wear the provided pressure garment for 3 hours in the morning, 3 hours in the afternoon, and 8 hours at night each day for 8 weeks.

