During Phase IA, i.e., the first four weeks between Time 1 (Baseline) and Time 2 (Week 4), when participants are hospitalized in the rehabilitation department of the hospital, he/she will be required to attend an occupational therapy session conducted by Therapist B once a day for 30 minutes, 5 days a week. During Phase IB, i.e., the second

four weeks between Time 2 (Week 4), and Time 3 (Week 8), when participants were being discharged from the hospital. Although they need to continually wearing the pressure garment according to same wearing schedule, they will not need to attend occupation therapy session.

Each participant will be given a Pressure Garment Application Form (Appendix K) to complete. The form will need to be returned to the researcher during Time 2 (Week 4) assessment. A new form will be given for the participant to complete and collected by the researcher during Time 3 (Week 8) assessment. Therapist B will constantly monitor the condition of the pressure garment to make sure it stays tightly fit throughout the study. Depends on the garment condition, torn or loosed pressure garment will be repaired or replaced using a new pair of garments.

For Time 2 (Week 4) and Time 3 (Week 8) assessments, the FMA, MAS, BBT, and VAS will be performed by Therapist A. The DASH and SF-36 will be administered by Therapist A and completed by the participant; however, if needed, it can be completed with the help of a caregiver or a therapist. The MAS will be assessed immediately after removal of the pressure garment, and the DASH, and SF-36 will be completed within 30 minutes of removal. The order of assessments will be determined by drawing a ballot. The FMA, BBT, VAS will be assessed 30 minutes after removal and the order of assessment will also be determined by drawing a ballot.

Phase IA = Pressure Garment + Occupational Therapy for 4 weeks

Phase IB = Pressure Garment for 4 weeks

Therapist B, a treating therapist will provide a list of specific occupational therapy interventions, identified in this study as representing routine practice to participants. Therapist B will record the Pressure Garment Application Form (Appendix K). These specific occupational therapy interventions will be given according to the following sequence:

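### The protocol's own steps leave the assessor's blinding unprotected: Therapist A fetches the randomisation number and rates MAS as soon as a distinguishable garment comes off

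*Protocol*

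**What the plan says.** Section 9.1.5 defines the role: "Therapist A, who will serve as an assessor and blinded". Section 9.1.4.3 names the "Fugl-Mayer Assessment of Upper Extremity as a primary outcome measure". At Weeks 4 and 8, "the FMA, MAS, BBT, and VAS will be performed by Therapist A"; Therapist A also administers DASH and SF-36.

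On allocation, Section 9.1.5 has the researcher generate "165 sequences that contains equal numbers of 1 (S-10), 2 (DD-10), and 3 (S-0" (closing bracket left off here). It continues: "After participant enrolment, Therapist A will report to the researcher to obtain the randomization sequence number generated using SPSS 26.0". The researcher then assigns the arm from the list, and Therapist A takes the baseline ratings, measures the arm and hands the measurements to the fabricator.

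On timing, the same section states: "The MAS will be assessed immediately after removal of the pressure garment". DASH and SF-36 fall within the first half hour after removal, and FMA, BBT and VAS come at half an hour.

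On appearance, Section 9.1.4.1.3 says that in DD-10 "the dorsal side is simply secured using two pieces of fabrics of the same size", and that its thumb is made differently from that of S-10. Section 9.1.4.1.4 says that S-0 is made in largely the same way as the single-layer garment, with zero reduction.

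At Week 8, participants and Therapist A are asked to guess the arm, and the answers are summarised with James' Blinding Index.

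**The concern.** The trial is presented as double-blind (Section 9.1.1), and S-0 exists to serve as placebo. That design protects the comparison only if the person scoring the outcome does not know the arm. FMA-UE and MAS both depend on the rater's judgement. The steps in Section 9.1.5 place the allocation number, and a garment that can be told apart in one of the three arms, within the assessor's reach, and no step takes them away again. If the assessor learns the arm, expectation can enter the primary comparison directly. Neither the intention-to-treat rule nor the imputation in Section 9.1.6 can remove it, and the ratings cannot be collected again.

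**Working it through.** No formula tests this point, so the check sets the steps side by side.

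**1. Who rates.** Therapist A rates FMA-UE, MAS and BBT at every visit. One person is therefore involved from garment removal through to the primary outcome.

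**2. The number.** The list consists of the values 1, 2 and 3, each tied to an arm. Therapist A obtains the sequence number after enrolment and before the baseline ratings. Taken literally, the number is one of those three values. It could also mean a position on the list, which reveals nothing. The text does not settle this and does not say that the number is masked.

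**3. The sight of the garment.** DD-10 differs from the other two by a second dorsal layer and by the thumb. S-10 and S-0 differ in reduction only, and no visible difference is described (the garment figures are not shown in the text at hand). The section does not say who removes the garment or where.

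**4. The two routes combined.**

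| Meaning of the sequence number | DD-10 against S-10 or S-0 | S-10 against S-0 |
|---|---|---|
| Arm code, key known | Exposed by number and by sight | Exposed by number |
| Arm code, key withheld | Exposed by sight; a few sightings also identify code 2 | Sorted into two unnamed sets, which noticing fit could name |
| Neutral list position | Exposed by sight | No documented route except noticing fit |

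On every reading, at least the DD-10 contrasts are unprotected.

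**5. Carry-over.** The immediate rating is MAS, a secondary outcome. FMA-UE comes half an hour later, but the rater is the same, and waiting does not remove knowledge.

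**6. Existing safeguard.** The guess questionnaire is given at Week 8, when follow-up is ending. Under the rule in Section 9.1.5, blinding is called lacking only if the upper confidence limit of the index is below 0.5; otherwise the plan concludes only that evidence of unblinding is insufficient. This measures a failure and does not prevent one.

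**7. How many participants.** Section 9.1.2.3 gives 44/(1 − 0.2) = 55 per arm, and 3 × 55 = 165, as stated. Sight could identify the 55 DD-10 participants, 55/165 = one third. The number, if it is the arm code and the key is known, reaches all 165. These are counts of exposure, not sizes of bias.

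**The case against.** The strongest reply is that the protocol calls Therapist A blinded again immediately after describing the collection of the number. That fits a neutral list position, with the researcher alone reading the arm from an electronically stored list. Someone other than the assessor might also remove the garment in practice, and assessor blinding is to be checked. The first part is a fair reading and limits the claim, but it supplies no safeguard: the text leaves open exactly the points on which blinding depends.

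A reader might infer several stronger things that the document does not support:

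- **That assessor blinding is already lost.** The ambiguity of the number and the silence on removal allow only that it is unprotected.
- **That the primary outcome is scored as the garment comes off.** That timing applies to MAS.
- **That S-0 is visibly loose.** Section 9.1.4.1.4 says only that wearers will not feel compression, and Section 9.1.5 has Therapist B keep garments tight without excepting S-0.
- **That measuring or training reveals the arm.** The section does say that "all the therapists will receive an 8-hour training on pressure garment from the pressure garment fabrication expert", but measurement precedes fabrication, and the reduction is applied to the measured value afterwards (Section 9.1.4.1.1). Training teaches garment types. It makes recognition of DD-10 easier and discloses no allocation.
- **That the fabricator may be Therapist A or B.** The fabricator is introduced as a further member of the study; that a therapist may fill the role does not make it one of these two.
- **That the bias can be given as a share of the targeted effect.** That would divide an assumed rater shift by an effect whose shape over time is also assumed.

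**Conclusion.** The point holds in this form: the protocol declares the assessor blinded, while its own steps on the randomisation number and on garment removal do not protect that status. The exposure by sight is documented for DD-10 against the single-layer garments. For S-10 against S-0 it rests on the number being the arm code, or on noticing fit. The size of any bias in FMA-UE or MAS cannot be derived from the document. The conclusion assumes that Section 9.1.5 will be followed as written and that no unstated masking step exists. Confidence that the gap exists is high; confidence that it would unblind the assessor in practice is moderate. It should be closed before enrolment, because the remedy is cheap and biased ratings cannot be repaired afterwards.

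**What to change.** Change two steps in Section 9.1.5.

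1. **Allocation.** The researcher sends the allocation directly to the fabricator. Therapist A receives and uses only an arm-neutral participant ID, including when passing on the measurements.
2. **Assessment at Weeks 4 and 8.** The garment is taken off and bagged before the participant meets Therapist A. The participant, a caregiver if there is one, or any on-site study member other than Therapist A can do this. MAS follows straight away, and participants are asked not to describe the garment to the assessor.

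Keep the Week 8 guess questionnaire as a check.

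The cost is mainly procedural wording. There is a short delay between removal and MAS, the same in all arms. Week 8 needs a small arrangement: participants have been discharged and no longer attend Therapist B's sessions, and Appendix A shows that not everyone will have a caregiver.

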James et al. (1996) proposed a BI, as a variation of the kappa coefficient, that is sensitive not to the degree of agreement but to the degree of disagreement, by placing the highest weight on 'do not know' responses. This index ranges from 0 to 1, 0 being total lack of blinding, 1 being complete blinding and 0.5 being completely random blinding (i.e. 50% correct and 50% incorrect guesses) (James et al. 1996). If the upper bound of the confidence interval (CI) of BI is below 0.5 (i.e., CI does not cover the null value), the study is regarded as lacking blinding (James et al. 1996). Otherwise, one may conclude that there is insufficient evidence for unblinding.

### **9.1.6 Data Analysis**

Data will be analysed using SPSS 26.0 using Intention-to-treat (ITT) analysis. ITT analysis, which aims to minimize bias and maintain random allocation of study participants (Gupta 2011), is suitable to be used when there are shedding participants. Its key idea is to analyse the group to which the participant belongs in that initial allocation, regardless of whether they completed the study or received the intended intervention. In clinical trials, participants may drop out, refuse intervention, or deviate from the study protocol. The ITT analysis includes all participants regardless of whether they completed the study or followed the treatment plan. This helps prevent shedding bias, which may occur if only completers are analysed (Mccoy 2017). The study will use a imputation method, such as, Last Observation Carried Forward (LOCF) (Shao & Zhong 2003) or mean imputation (Jadhav et al. 2019), or multiple imputation (Austin et al. 2021), this will probably depend on the requirements of the data.

Both descriptive and inferential statistics will be used. Frequencies, means, and medians will be used to describe the demographic data (Fisher & Marshall 2009). A mixed model ANOVA to compare the outcome measures.

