#### **9.1.2.3 Sample Size Calculation**

Sample size was calculated using G\*Power 3.1. Assuming that the data is normally distributed, this study will use mixed model ANOVA to compare differences between

the effects of DD-10, S-10, and S-0 pressure garment on sensorimotor functions and quality of life among stroke patients at three different time points during the 8 weeks of application. With small to medium effect size,  $f$  of 0.125, power of 0.8,  $\alpha$  error of 0.05, three groups, and three measurements, the total sample size needed will be 132, as shown in Figure 4. With 44 people in each group and taking into account the 20 % dropout rate, by using the formula:  $N = n/(1-d)$ , i.e.,  $44/(1-0.2) = 55$ , there will be a total of 55 people in each group. Thus, the final sample size will be 165 patients ( $n$ : DD-10 Group = 55; S-10 Group = 55; S-0 Group = 55).

[figure not shown]

Figure 4. Sample Size Calculation

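### The protocol treats LOCF, mean imputation and multiple imputation as interchangeable and fixes none; at the 20% dropout it allows for, each single-imputation option damages either the effect estimate or the error rate

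*Protocol*

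**What the plan says.** Section 9.1.6 of the protocol commits to intention to treat: "The ITT analysis includes all participants regardless of whether they completed the study or followed the treatment plan". For missing outcomes it then says "The study will use a imputation method, such as, Last Observation Carried Forward (LOCF"), "or mean imputation", "or multiple imputation", and closes with "this will probably depend on the requirements of the data". It does not say whether the mean is taken over all participants or within the arm. The analysis is "A mixed model ANOVA to compare the outcome measures".

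Section 9.1.2.3 sizes the trial for that analysis with an effect size "of 0.125, power of 0.8" and "error of 0.05, three groups, and three measurements". This gives 132 participants, raised to 165 for 20% dropout. The primary outcome is the upper-extremity Fugl-Meyer score (section 9.1.4.3), measured at baseline, Week 4 and Week 8.

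**The concern.** The protocol goes beyond leaving a detail to the statistical analysis plan. It names two single-imputation methods as acceptable alongside multiple imputation and ties the choice to the data.

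Three features of the design make this matter:

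- Participants enter 1 to 12 months after stroke (section 9.1.2.1), so scores may still be rising. LOCF freezes the score of anyone who leaves.
- Weeks 0 to 4 combine the garment with inpatient occupational therapy, while Weeks 4 to 8 are garment only, after discharge (section 9.1.5). For someone lost after discharge, LOCF reports a score from the therapy phase as the outcome of the later phase.
- Garments are worn 3 + 3 + 8 = 14 hours a day, and only S-0 is designed to feel uncompressed (section 9.1.4.1.4). Dropout could therefore differ by arm.

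Mean imputation adds values without spread and counts them as observed participants. At stake are the size of the primary comparison and its false-positive rate.

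**Working it through.** **The plan's own figure.** For the group-by-time F test, λ = f² × N × m / (1 − ρ). The text gives no ρ and Figure 4 is not shown, so I assume ρ = 0.5 and sphericity. Then λ = 0.125² × 132 × 3 / 0.5 = 12.375 with 4 and 258 degrees of freedom, and power is 0.808. This reproduces N = 132. Inflation: 44 / 0.8 = 55 per arm, 165 in total. The allowance is 165 − 132 = 33 participants, or 11 per arm.

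**Assumptions, none from the protocol.** Recovery is 0.4 SD per 4 weeks in every arm. The true difference between the extreme arms is 0.50 SD at Week 8, half of it present at Week 4. Dropout is non-informative within arm, and occurs either all after Week 4 or half before and half after.

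**Equal 20% dropout, expected Week 8 difference.**
- LOCF, all after Week 4: 0.8 × 0.50 + 0.2 × 0.25 = 0.45 (10% too small).
- LOCF, half before: 0.8 × 0.50 + 0.1 × 0.25 + 0.1 × 0 = 0.425 (15% too small). Simulation gave 0.42, a loss of 16%.
- Overall mean: 0.8 × 0.50 = 0.40 (20% too small). Simulation gave 0.395, a loss of 21%.
- Within-arm mean: 0.50 on average, so no bias in the estimate.

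**Equal 20% dropout, type I error of the group-by-time test** (simulated, 55 per arm, nominal 5%).
- LOCF 4.7% to 5.5%; overall mean 5.2%.
- Within-arm mean 8.6% with all dropout after Week 4, and 10.8% to 11.4% with half before.
- The reason for the last: the computed variance is about 0.8 of the true one and is divided by 55 instead of 44. The ratio of computed to true standard error is √(0.8 × 44/55) = 0.8. For a two-arm comparison at one visit, P(|Z| > 1.96 × 0.8 = 1.568) = 11.7%.

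**Dropout of 10/20/30% by arm, LOCF, no true effect.**
- All after Week 4: 0.4 × (0.30 − 0.10) = 0.08 SD false difference against the high-dropout arm.
- Half before: (0.15 × 0.8 + 0.15 × 0.4) − (0.05 × 0.8 + 0.05 × 0.4) = 0.12 SD.
- Simulation gave about 0.07 to 0.12 SD. With half the dropout before Week 4 and 60% of the recovery placed before it, type I error was 6.2% to 6.5% at ρ = 0.5 and 10.1% at ρ = 0.8.

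**Same dropout, true difference 0.50 SD in favour of the arm with 30% dropout, LOCF.**
- All after Week 4: (0.7 × 1.30 + 0.3 × 0.65) − (0.9 × 0.80 + 0.1 × 0.40) = 1.105 − 0.760 = 0.345.
- Half before: (0.7 × 1.30 + 0.15 × 0.65) − (0.9 × 0.80 + 0.05 × 0.40) = 1.0075 − 0.740 = 0.2675.
- If the better arm has the 10% dropout instead, LOCF exaggerates. All after Week 4: (0.9 × 1.30 + 0.1 × 0.65) − (0.7 × 0.80 + 0.3 × 0.40) = 1.235 − 0.680 = 0.555.

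**Open choice.** If all three methods were run and the smallest p-value kept, simulated type I error was 8.8% to 13.2% with the overall mean and 12.8% to 18.0% with the within-arm mean.

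**One multiple imputation fixed in advance.** Type I error was 4.2% to 6.0%, and the 0.50 SD difference was estimated at 0.50 to 0.51.

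**The case against.** A fair defence has four parts.

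- **The list is illustrative.** The wording is tentative, and the requirements of the data could mean the amount and pattern of missing values, judged blind. A statistical analysis plan may settle the rest. This stands in part: a reader might infer that the method will be picked after unblinded results are seen, but the text does not say so. It permits an open choice and sets no safeguard. The 9% to 18% range is a worst case, not a forecast.
- **Single imputation is not always invalid.** A reader might infer that LOCF and mean imputation inflate false positives as such. They do not: with equal dropout, LOCF and overall-mean imputation stay near 5%. The inflation to 9% to 11% needs within-arm means, which the protocol neither specifies nor excludes.
- **A larger inflation figure is available but does not apply.** Within-arm mean imputation gives about 16% for a stand-alone three-group comparison at Week 8. The protocol plans no such test, so that figure should not be used.
- **Unequal dropout is assumed.** The protocol states only the 20% allowance. The 30-minute try-on in section 9.1.5 may also remove some participants who would have left early because of the garment. This stands, and the unequal-dropout results are conditional on it.

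What remains is that the protocol itself endorses methods that fail on one measure or the other at its own dropout allowance.

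**Conclusion.** The point holds in this form: at 20% dropout, each single-imputation option that section 9.1.6 offers fails on either the estimate or the error rate, and the section gives no rule for choosing among them. LOCF and overall-mean imputation shrink a real difference by about 10% to 21% under equal dropout. Within-arm mean imputation roughly doubles type I error. When dropout differs by arm, LOCF also biases the comparison: a false 0.07 to 0.12 SD with type I error of about 6% to 10%, and a true 0.50 SD read as about 0.27 to 0.35 if the better arm loses more participants.

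These sizes rest on the assumed correlation, recovery, dropout timing and dropout imbalance. The direction of the LOCF bias depends on which arm loses more. The documents do not show that every option inflates false positives, or that anyone intends to choose the method from the results.

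**What to change.** In section 9.1.6, delete LOCF, mean imputation and the clause that leaves the choice to the data. Name one primary method before unblinding, either:

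- a likelihood-based repeated-measures mixed model with all observed baseline, Week 4 and Week 8 scores as outcomes, so that every randomised participant with a baseline score contributes and the three-measurement basis of the sample size is kept; or
- multiple imputation done by arm, including baseline, Week 4 score and hospital.

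The imputation model should not rely on wearing time. The wearing forms are collected at the Week 4 and Week 8 assessments (section 9.1.5), so they will tend to be missing for the same people whose outcomes are missing.

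A sensitivity analysis for data not missing at random is optional and can go in the statistical analysis plan. The cost is one paragraph of wording and slightly more analysis work. The sample size of 132, inflated to 165, does not change.
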